**STUDY SYNOPSIS**

**Aims:**

**1)** Assess the clinical feasibility and utility of biweekly β-D-glucan testing as a guide for preemptive antifungal therapy in at-risk surgical intensive care unit (SICU) patients.

1. Evaluate the safety and tolerability of preemptive anidulafungin as compared to current practice (empiric antifungal therapy based on physician discretion) for the management of invasive candidiasis (IC).
2. Validate gene expression signatures predictive of IC.

**Hypotheses:**

**1)** Biweekly β-D-glucan surveillance will identify SICU patients with an invasive fungal infection (IFI) before clinical signs or symptoms develop.

1. Anidulafungin initiated in response to a positive β-D-glucan test (i.e. preemptive therapy) will be well tolerated, safe, and effectively treat patients early, before advanced infection is established.
2. Peripheral blood gene expression signatures obtained serially from at-risk patients can predict early IC.

**Study Design:** Single center, randomized, non-blinded, parallel group, comparative study.

**Sample Size:** 100 subjects; 75 in the active surveillance/preemptive therapy arm and 25 in the usual care arm.

**Study Population:** Adult patients admitted to Duke University Medical Center SICU at-risk for the development of IC.

**Study Drug:** Intravenous anidulafungin initiated in response to a positive β-D-glucan test for subjects in the active surveillance/preemtpive arm. Preemptive treatment will continue for at least 14 days or until ICU discharge (maximum 28 days), which ever is longer.

**Efficacy:** IFI assessments will be made weekly and at SICU discharge.

**Safety:** A data safety monitoring board will review adverse events every 4 months.

**Statistics:** β-D-glucan test characteristics will be described using sensitivity, specificity, positive and negative predictive values. The proportions of patients developing proven or probable IC in each group will be compared using Fisher’s exact test. The prevalence of treatment emergent adverse events will be described using summary statistics. For gene expression analysis, we will designate subjects diagnosed with a *Candida* bloodstream infection as case patients and those who remained uninfected and had negative B-D-glucan testing as controls. Decision tree analysis will be used to develop predictive signatures for candidemia versus no infection.

**Chart of Study Procedures**

| **Procedure** | **Screening/Baseline** | **Weekly** | **Bi-weekly** | **Treatment** | **SICU Discharge** |
| --- | --- | --- | --- | --- | --- |
| **Informed Consent** | **X** |  |  |  |  |
| **Clinical Information** | **X^a^** | **X^a^** |  |  |  |
| **Physical Examination** | **X** |  |  | **X^b^** |  |
| **APACHE II Score Assessment** | **X** |  |  | **X** |  |
| **IFI Assessment^c^** | **X** | **X** |  |  | **X** |
| **Medication Review** | **X** | **X** |  |  |  |
| **Β-D-Glucan^d^** | **X** |  | **X** | **X** |  |
| **Fungal Culture^e^** | **X** |  |  | **X** | **X** |
| **Fungal Susceptibility^e^** | **X** |  |  | **X** | **X** |
| **Β-hCG** | **X^f^** |  |  |  |  |
| **LFTs^g^** | **X** |  |  | **X** |  |
| **RNA collection^h^** | **X** |  | **X** | **X** |  |
| **Blood Culture^i^** |  |  |  | **X** |  |

^a^Demographics, baseline conditions, pertinent past medical history at baseline followed by weekly assessment for evidence of IFI and for IC risk factors.

^b^Obtain within 72 hours of 1^st^ dose of study drug and weekly there after while receiving anidulafungin.

^c^ Vital signs, clinical signs and symptoms, routine laboratory tests, culture results, radiographic findings, and/or biopsy reports indicative of IFI.

^d^ Only BDG results for subjects in the active surveillance/preemptive therapy arm will be reported to clinicians in real-time. BDG testing for subjects receiving usual care will be performed in batches, retrospectively. Subjects on anidulafungin will have the BDG test performed every other day until negative to determine kinetics on therapy. Samples collected for BDG kinetics will be batch tested retrospectively, therefore the results will not be reported to clinicians.

^e^ Oral swish and spit or ETS aspirate (from those subjects requiring mechanical ventilation) to assess for fungal colonization will be performed at baseline, after the completion of any systemic antifungal therapy, and at SICU discharge. Susceptibility testing to echinocandins and fluconazole will be performed on each isolate recovered. Results will not be reported to the care providers.

^f.^ Pregnant women will be excluded from the study.

^g^ LFTs will be collected at baseline and weekly on anidulafungin. LFTs include: total bilirubin, alkaline phosphatase, AST, and ALT

^h^ Hybridization to microarrays will occur in selected patients with positive blood culture results (cases) and in controls (no positive blood cultures, no empiric antifungal therapy).

^i^Two sets of blood cultures will be obtained within 24 hours of a positive BDG test result if not already collected as a part of clinical care.

**List of Abbreviations and Specialist Terms**

| **Abbreviation or**  **specialist term** | **Explanation** |
| --- | --- |
| AE | Adverse event |
| BDG | (1→3) β-D-glucan |
| BSI | Blood stream infection |
| CFR | Case fatality rate |
| CRF | Case report form |
| DSM | Data safety monitor |
| EORTC/MSG | European Organization for Research and Treatment of Cancer/Mycoses Study Group |
| ETS | Endotracheal suction |
| FDA | U.S. Food and Drug Administration |
| GU | Genitourinary |
| HSCT | Hematopoietic stem cell transplant; for this report, includes all blood- and marrow-derived stem cell transplants |
| IC | Invasive candidiasis |
| IFI | Invasive fungal infection |
| IRB | Institutional Review Board |
| IV | Intravenous |
| LFTs | Liver function tests |
| LLN | Lower limit of normal |
| OD | Optical density |
| RNA | Ribonucleic acid |
| RTT | Response-to-therapy |
| SAE | Serious adverse event |
| SICU | Surgical intensive care unit |
| TPN | Total parentral nutrition |
| SOT | Solid organ transplant |
| ULN | Upper limits of normal |
| WNL | Within normal limits |

**INTRODUCTION**

**Epidemiology of Invasive Candidiasis**

Fungal infections are devastating to human health and have lethal consequences for both immunocompromised and critically ill patients in the Intensive Care Unit. *Candida* species are now the 4^th^ most common cause of bloodstream infection in the United States (1), with the vast majority of these infections being nosocomially acquired(2). Most *Candida* blood stream infections (BSIs) are due to *C. albicans* followed in frequency by *C. glabrata*, a species that is generally less susceptible to traditional antifungal therapy (i.e., fluconazole). Despite the availability of newer antifungal drugs, the mortality attributable to invasive candidiasis (IC) remains extremely high (3). One reason that IC is so devastating is the difficulty in establishing a timely diagnosis. The clinical presentation of IC is highly variable and nonspecific, and standard blood culture is notoriously insensitive. In addition to the clinical impact, IC is a burden on the healthcare system, with estimates of increased costs on the order of $40,000 US dollars per episode(4;5).

Patients in the ICU have a higher incidence of *Candida* BSI as compared to those on general medical/surgical wards(1). Given that IC carries such a high associated morbidity, mortality, and cost, prophylactic antifungal therapy has been proposed as a way to prevent disease in high-risk patient populations. Azoles and polyenes have both been studied as prophylaxis in the ICU setting and were shown to decrease the incidence IFIs without impacting overall mortality(6-10). Individual prophylaxis studies, however, have varied widely with regard to patient selection and antifungal regimen. No consensus on the optimal preventative strategy currently exists, but experts have advocated some form of antifungal prophylaxis in situations where the rate of IC is expected to approach 10%(11).

**Issues Regarding Clinical Trials of Antifungal Prophylaxis**

Two key points of interest for future studies of IC prophylaxis are the choice of antifungal agent and the definition of patient risk. In terms of drug selection, the polyenes are limited by drug-associated toxicities and the azoles have been suspected of promoting a shift toward more resistant, non-*albicans* species(10). The echinocandins are the newest class of antifungal agents. The group is active against a broad range of *Candida* species, have relatively few drug-related toxicities/interactions, and would likely be effective as prophylaxis(12). As of yet, an echinocandin has not been studied for prophylaxis in the ICU setting. Many clinical risk factors for IC have been identified (**Table 1**), but their predictive value is uncertain(7). Risk-factor based prediction rules for the identification of individual patients at highest-risk for IC are typically complicated, too cumbersome and impractical to use in clinical practice, and may be too restrictive to use as enrollment criteria for clinical trials of antifungal prophylaxis. In fact, previous ICU prophylaxis studies that based inclusion on the presence of multiple clinical risk-factors closed prematurely due to difficulties identifying eligible patients in addition to the overall reluctance of clinicians to enroll high-risk patients in to a study with a placebo control arm.

**Preemptive Antifungal Therapy Based on Fungal Biomarkers**

β-D-glucan (BDG) is a cell wall constituent found in many pathogenic fungi including *Aspergillus* and *Candida* as well as *Fusarium*, *Trichosporon*, *Saccharomyces,* and *Acremonium*. Assays that are capable of detecting BDG in the serum of patients with IFI due to these organisms have been developed commercially. The β-D-glucan test (Fungitell^™^; Associates of Cape Cod, Falmouth, MA) is FDA approved as an adjunct to the diagnosis of deep-seated mycoses and fungemia. BDG analysis performed on serial serum samples obtained from 283 patients with acute myeloid leukemia or myelodysplastic syndrome who were receiving antifungal prophylaxis revealed that the test became positive a median of 10 days before the clinical diagnosis of IFI in 100% of patients(13). Absence of a positive test result had a 100% negative predictive value and a single positive test result had a specificity of 90%.

Primary prevention strategies that incorporate serial measurement of fungal biomarkers with initiation of antifungal therapy in response to a positive test represent an exciting new approach to IC management. Early initiation of appropriate antifungal therapy has been shown to improve clinical outcomes, but to date, the BDG assay has only been validated for patients with hematological malignancies and/or following transplantation. The performance of the test in the ICU setting has not been established. Poor specimen handling, hemodialysis using certain cellulose membranes, exposure to gauze products, some antibiotics, and recent receipt of albumin or immunoglobulin products may cause false positive test results in some patients(14-18). Since many of these potential sources of BDG cross-reactivity are present in the ICU population (**Table 2**), further investigation of the assay is warranted in this setting.

**Anidulafungin**

Until recently, the treatments available for serious fungal infections were limited to either amphotericin products (polyenes) or the azoles. Each class demonstrated significant limitations. The echinocandins are a new class of antifungal agents that appear to have several advantages over existing drugs. The echinocandins include 3 compounds: caspofungin, micafungin, and anidulafungin. Current evidence suggests that the three drugs are equivalent with regard to spectrum of activity, pharmacokinetics, drug interactions, and side effects. As a class, the echinocandins are active against *Candida* and *Aspergillus,* including species that are resistant to traditional antifungal agents. Primary or secondary drug resistance to the echinocandins is exceedingly rare. In addition, these compounds have demonstrated excellent clinical safety and efficacy as well as a more favorable toxicity profile than either amphotericin based products or the azoles(19).

Anidulafungin (Eraxis™, Pfizer) is the newest echinocandin to be approved by the FDA and has been studied for the treatment of esophageal candidiasis, candidemia, and deep-tissue IC. The drug works through the noncompetitive inhibition of (1,3)-β-D-glucan synthase(20), does not require dose adjustments in subjects with hepatic or renal impairment(21), and has demonstrated a low rate of adverse events in the phase 2/3 trials conducted to date. The drug is not a substrate, inducer, or inhibitor of cytochrome P450 and is therefore unlikely to affect the metabolism of other drugs that use these isoenzymes. Histamine-mediated symptoms have been reported during anidulafungin infusion including rash, urticaria, flushing, puritis, dyspnea, and hypotension, but are infrequent when the rate of infusion does not exceed 1.1 mg/minute. Laboratory abnormalities in liver function tests (LFTs) have also been seen in patients treated with anidulafungin, but the clinical significance of this observation is uncertain. Hepatic metabolism of anidulafungin has not been observed. Rather, the drug undergoes slow chemical degradation and is excreted primarily in feces(22).

Of the echinocandins, only micafungin has been studied as IFI prophylaxis(12). In a multi-center randomized trial, this agent was more effective than fluconazole (difference 6.5%, 95% CI: 0.9 – 12%) for the prevention of suspected, proven, or probable IFI during the Neutrogena period following hematopoietic stem cell transplant (HSCT)(12). The drug was safe and well tolerated as prophylaxis in this trial.

**Gene Expression Profiling to Diagnose Infectious Diseases**

The challenge for clinicians in diagnosing IC is both the delay in culture positivity as well as the relative insensitivity of blood cultures. The use of microarray technology to establish gene expression signatures unique to pathogens in parallel with established techniques may help quickly classify the cause of patient illness. Once the gene expression signatures are established, a rapid assay can be developed using multiplex PCR technologies. Such an assay would be used to target antimicrobial therapy and could be a valuable adjunct to pathogen based tests such as the BDG assay.

There is substantial evidence that different infectious agents trigger unique gene expression signatures in host immune effector cells both in vitro and in vivo. Gene expression in white blood cells provides direct analysis of early host response to invasive pathogens. Evaluation of these expression profiles provides not only a diagnostic opportunity, but also information regarding key elements of host response to a variety of pathogen classes. *In vitro* stimulation of human PBMCs with bacteria and bacterial products results in gene expression patterns that are pathogen specific(23). Members of our research group have identified gene expression signatures that can differentiate between typhus and paratyphus infections that cause a febrile illness that is otherwise clinically indistinguishable using a well-characterized Nepalese cohort (unpublished data). Researchers have also described gene expression patterns associated with viral(24) and fungal infections. These studies support the concept that identification of global changes in the gene expression patterns of PBMCs can be used to differentiate between major infectious causes of illness and can provide clinically meaningful classification of pathogens in patients.

**STUDY OBJECTIVES**

The main goal of this study is to evaluate the feasibility and safety of a preemptive antifungal treatment strategy, incorporating twice weekly BDG testing, as compared to an empiric approach (standard care) for the management of IC in at-risk adult SICU patients.

**Primary Objectives**

1. Determine the feasibility of preemptive antifungal treatment in an academic SICU setting
2. Define β-D-glucan test performance in the Duke SICU patient population
3. Evaluate the safety and tolerability of preemptive anidulafungin

**Secondary Objectives**

1. Compare the prevalence of IC between treatment groups (i.e., preemptive versus standard empiric therapy)
2. Compare the duration of SICU stay by treatment group
3. Compare the number febrile days by treatment group
4. Compare antifungal drug utilization between treatment groups
5. Compare the overall mortality rate between treatment arms at SICU and hospital discharge
6. Evaluate clinical response to preemptive or empiric antifungal therapy
7. Compare the prevalence of fungal colonization by group at baseline, at the end of antifungal therapy, and at SICU discharge
8. Determine the susceptibility of fungal pathogens identified (if any) and compare between groups
9. Assess the number of breakthrough IFIs in each management arm
10. Assess premature withdrawals from assigned strategy
11. Compare costs (antifungal drugs + diagnostic testing) between the 2 strategies
12. Obtain RNA from this well-characterized cohort of patients at-risk for the development of IC to derive gene expression signatures that characterize early candidemia

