**Stratification and Randomization**

Patients who meet inclusion/exclusion criteria and provide written informed consent will be stratified into 2 groups based on APACHE II score. Group 1 will have APACHE II scores ≤ 20 and group 2 > 20. Subjects within each APACHE II group will then be assigned to either active surveillance with preemptive anidulafungin based on a positive BDG test or standard care using a 3:1 randomization schedule (approximately 75 subjects in the preemptive group and 25 in the standard care group). The study coordinator will assign each patient to the next available randomization number which will be generated using randomization software. Patient study identification (ID) numbers will also be assigned sequentially starting with Patient No. 1. Dropouts will not be replaced.

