**Screening/Baseline**

Procedures must be performed within 3 days prior to randomization:

- **Signed informed consent prior to the performance of any study-specific procedures.**
- Complete medical and medication history, including a prior antifungal therapy review.
- Complete physical examination including vital signs.
- Liver function tests will be drawn if not already done as a part of standard care in the preceding 3 days.
- Calculate APACHE II score (<http://www.sfar.org/scores2/apache22.html>)
- Oral wash or ETS for semi-quantitative fungal culture with susceptibility testing.
- B-HCG test for women of childbearing age if not already done as a part of standard care (<60 years old)

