**Secondary Endpoints**

1. Prevalence of IC by treatment group (i.e., preemptive therapy versus standard care).
2. Duration of SICU stay by treatment group.
3. Number febrile days by treatment group.
4. Antifungal drug utilization by treatment group.
5. Overall mortality rate between treatment arms at SICU and hospital discharge.
6. Response to preemptive or empiric antifungal therapy will be assessed.
7. Fungal colonization rate by group at baseline, at the end of antifungal therapy, and at SICU discharge.
8. Susceptibility of fungal pathogens identified (if any).
9. Number of breakthrough IFIs by group.
10. Number of premature withdrawals from assigned strategy.
11. Costs (antifungal drugs + diagnostic testing) by group.
12. Gene expression signatures related to early candidemia (prior to blood culture positivity) and late candidemia (after blood culture positivity) and no candidemia (negative blood culture and negative B-D-glucan testing).

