**STATISTICAL METHODOLOGY**

**Sample Size**

Targeted enrollment is 100 adult SICU patients. This study will not be powered to show a difference in the efficacy of preemptive management versus standard care due to single center population constraints in addition to cost limitations. Sample size calculations were therefore based on the number of adult patients expected to be admitted to the SICU over a 1 year period who are likely to meet inclusion criteria (n=700). Based on prior experience, it is reasonable to expect an accrual of 100 patients in a year. Using a 3:1 randomization strategy, 75 will be assigned to active surveillance and 25 to standard care. We estimate that 25% of patients will develop a positive test(13;25;27) and 19 will receive anidulafungin. These numbers should provide sufficient data for a preliminary feasibility evaluation of the preemptive strategy.

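### Baseline colonization, measured before randomisation, is listed as a between-arm comparison, and the discharge comparison is worded without using each patient's own baseline culture

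*Protocol*

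**What the plan says.** Protocol, Secondary Objectives, item 7: "Compare the prevalence of fungal colonization by group at baseline, at the end of antifungal therapy, and at SICU discharge". Secondary Endpoints, item 7, gives the same three times without the verb: "Fungal colonization rate by group at baseline, at the end of antifungal therapy, and at SICU discharge".

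The baseline specimen is listed under Screening/Baseline as "Oral wash or ETS for semi-quantitative fungal culture with susceptibility testing", and that list opens with "Procedures must be performed within 3 days prior to randomization". A footnote to the Chart of Study Procedures confirms the sampling times: the culture "will be performed at baseline, after the completion of any systemic antifungal therapy, and at SICU discharge".

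On design, the Sample Size section states "Targeted enrollment is 100 adult SICU patients" and "Using a 3:1 randomization strategy, 75 will be assigned to active surveillance and 25 to standard care". Randomisation is stratified on severity alone: "Group 1 will have APACHE II scores ≤ 20 and group 2 > 20".

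The Statistical Analyses section provides a Chi-squared test for discrete baseline characteristics, Fisher's exact test for IFI and IC, and the Kruskal-Wallis test for ICU stay and febrile days. It assigns no method to colonization.

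**The concern.** Two things in the wording are unhelpful.

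First, baseline stands beside two post-randomisation times as an occasion for comparing the arms. Since the culture precedes randomisation, any difference there is chance and says nothing about the strategy. Imbalance in baseline characteristics is already covered elsewhere in the Statistical Analyses section.

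Second, the discharge endpoint is framed as prevalence by group. The same type of specimen is planned at baseline and at discharge, so a patient's own baseline result is a natural predictor of the discharge result, yet neither the objective nor the endpoint uses it. Prevalence at discharge also combines persistence in patients who arrived colonised with new acquisition in those who did not, and these are different questions.

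With only 25 standard-care patients and no balancing on colonization, the arms may differ noticeably at baseline. Whoever reads the discharge difference would then have to guess how much of it was inherited.

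**Working it through.** **Inputs from the Protocol.** N = 100, allocated 3:1; stratification by APACHE II only; two-sided 5% level. The stated arm sizes reproduce: 100 × 3/4 = 75 and 100 × 1/4 = 25. So does the expected number treated: 0.25 × 75 = 18.75, given as 19. No sample size, power or effect size is stated for colonization.

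**Assumptions, not in the Protocol.** Baseline colonization prevalence p, shown for 20%, 30% and 50%. Correlation ρ between a patient's baseline and discharge status, shown for 0.3, 0.5 and 0.7. Prevalence is taken as equal at the two times when there is no strategy effect, so the regression slope equals ρ.

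**Step 1: size of the chance baseline difference.** SD = √[p(1−p)(1/75 + 1/25)]. For p = 0.5 this is √(0.25 × 0.0533) = 0.1155. The probabilities are exact binomial.

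| p | SD, 75:25 | SD, 50:50 | P(gap ≥ 10 points) | P(gap ≥ 15) | P(gap ≥ 20) |
|---|---|---|---|---|---|
| 20% | 9.2 points | 8.0 | 28% | 10% | 3.5% |
| 30% | 10.6 | 9.2 | 35% | 15% | 6.7% |
| 50% | 11.5 | 10.0 | 39% | 19% | 9.4% |

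**Step 2: what carries to discharge.** The expected carry-over is ρ times the baseline gap. A 20-point gap carries 6, 10 or 14 points into the unadjusted discharge difference at ρ = 0.3, 0.5 or 0.7.

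**Step 3: precision given up.** Adjusting for baseline multiplies the variance by 1 − ρ² and the standard error by √(1 − ρ²). The last column is 100/(1 − ρ²), the unadjusted sample size with the same precision as 100 patients analysed with adjustment.

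| ρ | Variance ratio | SE ratio | SE reduction | Equivalent unadjusted N |
|---|---|---|---|---|
| 0.3 | 0.91 | 0.954 | about 5% | about 110 |
| 0.5 | 0.75 | 0.866 | about 13% | about 133 |
| 0.7 | 0.51 | 0.714 | about 29% | about 196 |

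Simulation with 40,000 trials per setting (p = 0.3 and 0.5) gave SE ratios of about 0.96, 0.87 and 0.72, in agreement.

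**Step 4: validity of the unadjusted test.** In the same simulations, with no strategy effect, the unadjusted test rejected in 4.8% to 5.5% of all trials, which is close to nominal. Among only those trials with a baseline gap of at least 15 points, it rejected in about 8%, 12–13% and 19–20% at ρ = 0.3, 0.5 and 0.7.

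**The case against.** The strongest reply is that the Protocol does not prescribe a crude comparison. A reader might infer from the objective that discharge colonization will be tested unadjusted, but the Statistical Analyses section names no method for it and does not exclude adjustment. Covariate adjustment of a secondary endpoint is commonly left to an SAP, and none is shown here. That stands: the point concerns what the objective and endpoint are worded to estimate, not a missing method.

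A reader might also infer that the unadjusted comparison is biased or has inflated error. It is neither. Randomisation makes it unbiased on average, and its overall type I error is about 5%. The higher rejection rates in step 4 apply only after selecting trials with a large baseline gap. They matter when interpreting the one imbalance that actually occurs; they do not show that the test is invalid.

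It is fair, too, that the endpoint wording, unlike the objective, does not use the verb compare and can be read as description over time. Showing colonization by arm at baseline is useful context, since Table 1 lists *Candida* colonization at multiple sites as a risk factor for IC. Description is worth keeping; only its status as a between-arm comparison should go.

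Finally, the size of the gain rests on assumed values, and at ρ = 0.3 it is small. No gain in power can be claimed: the Protocol gives no effect size for colonization, states that it is not powered for efficacy, and expects only about 19 of the 75 preemptive-arm patients to receive study drug.

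**Conclusion.** The point holds as a modest improvement. Both item 7 entries place a pre-randomisation measurement among the times of a between-arm endpoint, and neither uses it where it would help, at discharge. That follows from the text and needs no assumption.

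The size does need assumptions. If baseline prevalence is 20% to 50%, chance alone gives a baseline difference with an SD of about 9 to 11.5 points, and a gap of 15 points or more in 10% to 19% of trials. If the baseline-discharge correlation is 0.3 to 0.7, ignoring baseline forgoes a 5% to 29% reduction in standard error.

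This is item 7 of 12 secondary endpoints in a feasibility study. The primary endpoints (feasibility, test performance and safety) do not depend on it.

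**What to change.** In Secondary Objectives item 7 and Secondary Endpoints item 7:

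- Report baseline colonization by arm descriptively, with no between-arm test.
- Compare colonization at SICU discharge stratified by, or adjusted for, the patient's own baseline culture, for example as a Mantel-Haenszel risk difference with 95% CI. Include the APACHE II randomisation stratum where numbers allow.
- Report new colonization among baseline-negative patients and persistence among baseline-positive patients by arm, as descriptive estimates with confidence intervals.

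The cost is small: the change is to wording, and the baseline culture is already planned for every patient. There are two drawbacks. Patients without a baseline specimen must be flagged and their handling stated. The subgroup estimates will also be imprecise: at an assumed prevalence of 20% to 50%, the 25 standard-care patients would include only about 5 (25 × 0.2) to 12 or 13 (25 × 0.5) who are colonised at baseline, which is why those estimates should be descriptive.
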